##### Statistical analysis

The statistical significance of ERP components will be tested by comparing their mean amplitudes to zero at ROIs using one-sample t-tests. This method will allow us to focus exclusively on significant responses, and to distinguish significant scalp distributions from noise. Statistically significant ERPs will be considered for further amplitude analysis.

For standard stimuli, levels of naturalness comparisons will be performed by Level × ROI repeated measures ANOVAs on each ERP and group independently. For deviant stimuli, Level × ROI × Deviant repeated measures ANOVAs will be performed.

Group comparisons will be conducted by Group × ROI repeated measures ANOVAs on each ERP and level of naturalness separately, for standard stimuli. Similarly, for deviant stimuli, Group × ROI × Deviant repeated measures ANOVAs will be performed. The effect of reducing the naturalness of voice on emotion processing will be assessed by the comparison between ERPs amplitudes at levels 1–5 for ASD group and ERPs amplitudes calculated in the control group for human voices. We expect to detect less natural voices to help typical processing in ASD children, that is, fewer difference with non-pathological processing of human voices at least natural voices. Based on MMN analysis at maximum peak ROI, the voice leading to the nearest to non-pathological processing in autistic children will be chosen for Stage 3.

Scalp distribution comparisons for standard stimuli will be assessed by Group × Laterality (FP1, F3, F7, T7, C3, P3, P7, O1/AFz, Fz, CPz, Cz, POz, Pz/FP2, F4, F8, T8, C4, P4, P8, O2) repeated measures ANOVAs on each ERP and level of naturalness separately. For deviant stimuli, Group × Laterality × Deviant repeated measures ANOVAs will be conducted.

For all amplitude analysis, normality will be assessed by Shapiro–Wilk test. In case of non-parametric distribution of the data, a transformation will be applied. Mauchly’s test of sphericity will be used to evaluate homogeneity of variances and co-variances. In case of violation of sphericity, a Greenhouse-Geisser correction will be applied in order to test main effects significance. *Post hoc* comparisons will be conducted to assess specific differences (Tukey and Dunnett procedures). In all cases, level of significance will be set at *p* < 0.05 and statistical analysis will be performed with R software.

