#### Data Analysis

For ERP amplitude analysis, electrodes will be grouped according to regions of interest (ROIs). Left prefrontal site: FP1. Left frontal channels: F3, F7. Right prefrontal site: FP2. Midline pre-frontal site: AFz. Midline frontal electrode: Fz. Right frontal channels: F4, F8. Left temporal site: T7. Left central electrode: C3. Midline central electrode: Cz. Right temporal site: T8, Right central electrode: C4. Centro-parietal electrode: CPz. Left parietal sites: P3, P7. Midline-parietal electrode: Pz. Right parietal sites: P4, P8. Midline parieto-occipital electrode: POz. Left occipital site: O1. Right occipital site: O2. Maximum peak time window analysis will be: 100–250 ms for the MMN (Kujala et al., 2007; Paris et al., 2018), 170–230 ms for P200 component (Paulmann et al., 2013), 200 and 350 ms for the P3a (Kujala et al., 2007; Paris et al., 2018), and 400–1,000 ms for the LPP component (Steber et al., 2020).

Event-Related Potentials will be extracted by averaging the data obtained for standard and deviant stimuli, and for each condition independently. The ERPs elicited by standard stimuli will be subtracted from the ERPs elicited by deviants to calculate difference waves. The mean ERPs amplitude will be calculated as follows. For standard stimuli, level of naturalness and group average peak latencies will be determined from all ROIs. Mean amplitudes will be determined by considering a ±50-ms time window centered at the grand mean peak latency. For deviant stimuli, mean amplitudes will be calculated from the difference waves at ROIs. Mean amplitudes will be determined by considering a ±50-ms time window centered to the grand mean peak latency (Kujala et al., 2007; Paris et al., 2018).

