##### Statistical analysis on ERPs data

The statistical significance of ERP components will be tested by comparing their mean amplitudes to zero at ROIs using one-sample *t*-tests. This method will allow us to focus exclusively on significant responses, and to distinguish significant scalp distributions from noise. Statistically significant ERPs will be considered for further amplitude analysis.

Group comparisons will be conducted by Group × ROI repeated measures ANOVAs on each ERP and assessment session separately, for standard stimuli. Similarly, for deviant stimuli, Group × ROI × Deviant repeated measures ANOVAs will be performed.

For standard stimuli, time comparisons will be conducted by Assessment Session × ROI repeated measures ANOVAs on each ERP and group separately. For deviant stimuli, Assessment Session × ROI × Deviant repeated measures ANOVAs will be performed.

Scalp distribution comparisons for standard stimuli will be assessed by Group × Laterality (FP1, F3, F7, T7, C3, P3, P7, O1/AFz, Fz, CPz, Cz, POz, Pz/FP2, F4, F8, T8, C4, P4, P8, O2) repeated measures ANOVAs on each ERP and assessment session separately. For deviant stimuli, Group × Laterality × Deviant repeated measures ANOVAs will be conducted.

For all amplitude analysis, normality will be assessed by Shapiro–Wilk test. In case of non-parametric distribution of the data, a transformation will be applied. Mauchly’s test of sphericity will be used to evaluate homogeneity of variances and co-variances. In case of violation of sphericity, a Greenhouse-Geisser correction will be applied in order to test main effects significance. *Post hoc* comparisons will be conducted to assess specific differences (Tukey procedure).

All statistical analysis will be performed with R software. Level of significance will be set at *p* < 0.05.

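### The one-sample t-tests said to separate scalp responses from noise are run at 18 ROIs at p < 0.05 without correction, so noise alone will often yield a significant ROI

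*Protocol article*

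**What the plan says.** The Stage 2 Data Analysis section groups the electrodes into ROIs and lists them. It gives peak search windows of 100–250 ms (MMN), 170–230 ms (P200), 200–350 ms (P3a) and 400–1,000 ms (LPP). For standard stimuli, "level of naturalness and group average peak latencies will be determined from all ROIs". The amplitude is then taken around that peak: "Mean amplitudes will be determined by considering a ±50-ms time window centered at the grand mean peak latency". For deviants the same ±50 ms rule is applied to the difference waves, without saying over which groups or levels the grand mean is formed.

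The Stage 2 Statistical analysis section says that components will be "tested by comparing their mean amplitudes to zero at ROIs using one-sample t-tests". It states the purpose: "This method will allow us to focus exclusively on significant responses, and to distinguish significant scalp distributions from noise". ERPs that are significant go on to the amplitude ANOVAs. On the level it says: "In all cases, level of significance will be set at *p* < 0.05". Tukey and Dunnett are named there, but only for post hoc comparisons.

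Stage 3 repeats the scheme under Statistical analysis on ERPs data: "The statistical significance of ERP components will be tested by comparing their mean amplitudes to zero at ROIs", with the same statement of purpose and the same level.

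**The concern.** The article says what the screening step achieves: it tells real scalp distributions from noise. A set of 18 tests, each at 5%, does not do that. When no response exists, 18 × 0.05 = 0.9 ROIs per component are expected to be significant by chance, in each group and level.

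A second, smaller problem is that the measurement window may be placed at the largest excursion of the data that are then tested against zero. This matters where the search window is long compared with the 100 ms measurement window, as for the LPP (600 ms).

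At stake is the description of which components are present and where on the scalp, in autistic and typically developed children. A component may be reported as present, or kept for analysis, because of noise.

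**Working it through.** The article states no error rate for this step, so there is no figure to reproduce.

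**Inputs**
- ROIs, counted from the Stage 2 Data Analysis list: FP1; F3/F7; FP2; AFz; Fz; F4/F8; T7; C3; Cz; T8; C4; CPz; P3/P7; Pz; P4/P8; POz; O1; O2. Total 18.
- Level per test: 0.05. Two-sided is assumed, as sidedness is not stated.
- Participants per cell: in Stage 2, 40 per group, each hearing 3 of 6 blocks, so on average 40 × 3/6 = 20 per group and level. In Stage 3, 18 per group.
- Inter-ROI correlation under noise: not in the article, so a range of 0 to 0.9 is used. The only correlation given is 0.5 among repeated measures, for sample size.
- Passing rule: not stated. One significant ROI is assumed to suffice.

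**Step 1. Multiplicity alone (fixed window, pure noise)**

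With independent ROIs: 1 − 0.95^18 = 0.603. For correlated ROIs, one-sample t-tests were simulated with equal correlation between all pairs:

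| Inter-ROI correlation | Chance of at least one significant ROI |
|---|---|
| 0 | 60% |
| 0.3 | 51% |
| 0.5 | 41% |
| 0.7 | 29% |
| 0.8 | 22% |
| 0.9 | 15% |

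Runs with 18, 20 and 40 participants agree closely (at correlation 0.5: 0.42, 0.40 and 0.40), so the table serves both stages. Even at 0.9 the rate is three times the nominal 5%.

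**Step 2. Adding the peak-centred window**

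Noise recordings with 18 correlated ROIs, baseline-corrected, were simulated. The window was centred on the group-average peak of the same data, respecting each component's polarity.

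| Inter-ROI correlation | MMN, P200, P3a: at least one ROI | LPP: at least one ROI |
|---|---|---|
| 0.5 | 39–46% | 44–53% |
| 0.8 | 22–28% | 24–40% |
| 0.9 | 13–21% | 19–27% |

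Per ROI, the rate stays near 5% for MMN, P200 and P3a. For the LPP one set of simulations gave 6–9% at correlations of 0.5 and above, and a separate check gave 7–11%. The LPP reaches 12–18% only if the peak may have either sign. Most of the excess therefore comes from Step 1.

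**Step 3. Effect of a correction**

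At a threshold of 0.05/18 = 0.0028 with independent ROIs: 1 − (1 − 0.05/18)^18 = 0.049. Holm starts from the same threshold, so when all 18 ROIs are noise it gives the same chance of any false positive. With the peak-centred window kept, this threshold gives about 0–7% when the peak is taken from the mean over ROIs. When it is taken from the largest ROI, it gives about 0–8% for MMN, P200 and P3a and up to about 11% for the LPP. The LPP thus also needs a latency not chosen on the data under test.

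**The case against.** **A condensed article.** Correction details for a preliminary test often sit in a fuller analysis plan. That would answer a complaint of omission. Here the article itself fixes the test, the level and the use of the result, and says what the step achieves. It names Tukey, Dunnett and Holm elsewhere, but only for post hoc tests. The stated property is wrong as written.

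**The later ANOVAs.** A reader might infer that noise passing the screen raises the false-positive rate of the Group, Level, Session and Laterality ANOVAs. The document does not support that. A screen can only remove ANOVAs: the probability that an ANOVA rejects and the screen passes cannot exceed the probability that it rejects. Nor does the text say that single ROIs are dropped. The ANOVAs run on each ERP with ROI as a factor, and the Stage 3 voice is chosen from the MMN at the maximum-peak ROI.

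**Peak-centring as a main fault.** A reader might also infer this. It adds almost nothing for the MMN. For deviants the grand mean may already be pooled over groups and levels, which would remove part of the effect. What stands is a caveat for the LPP.

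**Total counts.** Multiplying ROIs, components, groups, levels or sessions, and stimulus types gives thousands of tests. The text does not define that cell structure, and an MMN on standard stimuli alone is doubtful, so no total is claimed.

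**Assumptions.** The percentages depend on a correlation and a passing rule that the article does not give. That stands and is carried into the conclusion.

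**Conclusion.** The concern holds in limited form. The claim that these t-tests separate scalp distributions from noise fails at every correlation examined. For one component in one group and level, the chance of at least one false ROI runs from about 60% (independent) to 15% (correlation 0.9), against a nominal 5%. These figures rest on two-sided tests, equal correlation between ROIs, and one significant ROI being enough; a stricter passing rule would lower them. The LPP carries a modest further inflation per ROI.

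The consequence is descriptive: noise may be reported as a significant response, and components may be retained for the wrong reason. The point should be corrected, but it does not undermine the group, level or session comparisons as such.

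**What to change.** 1. Within each component's test against zero, apply a Holm or max-t permutation correction over the 18 ROIs, in both stages. State how many ROIs must be significant for a component to go forward.
2. For the LPP, take the peak latency from an average pooled over groups and levels (Stage 2) or groups and sessions (Stage 3), or use a pre-set window. Whole-window means are not advised for the other components: P200 (170–230 ms) lies inside the MMN window (100–250 ms) and P3a starts at 200 ms, so such means would mix them.
3. Delete or reword the sentence, in both stages, saying that the t-tests distinguish scalp distributions from noise.

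The cost is analysis wording and a standard routine; recruitment and recording do not change. The downside is somewhat less sensitivity to weak true responses confined to single ROIs, and slightly less latency tuning per group for the LPP. Max-t loses less than Holm when ROIs are strongly correlated.

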### EEG Signature of Emotion Recognition

To record the brain signature of emotions differentiation in voice, soundless methods may be more suitable since the recording process does not interfere with the acoustic stimulus that has to be processed. EEG, and particularly the analysis of Event-Related Potentials (ERPs), has been widely used to study the neuronal activation process of emotions. Furthermore, thanks to its high temporal resolution, ERPs analysis enable the distinction within attentional, sensory, and higher cognitive stages (Fan and Cheng, 2014). Early automatic auditory perception is usually observed between 100 and 250 ms over frontal and central cortices after stimulus onset (MMN). Higher amplitude of this component indicates higher discrimination of acoustic modulations relative to constant auditory background (Charpentier et al., 2018). As an index of acoustic changes early discrimination, the MMN can be used as an indicator of emotional prosody detection (Lindström et al., 2016, 2018; Paris et al., 2018). If automatic changes discrimination was salient enough, involuntary attentional switch to deviant auditory stimuli happens, and is observed 200–350 ms after stimulus onset at fronto-central cortices as a component known as P3a (Lindström et al., 2018; Paris et al., 2018). Early emotional recognition, valence, and arousal identification appear over frontal and central electrodes between 250 and 350 ms after the stimulus onset (Paulmann et al., 2013). The analysis of the amplitude of the P200 component has allowed to distinguish different prosodies such as disgust (high amplitude) and fear (lower amplitude) (Paulmann et al., 2013). This component has shown to reflect the early arousal decoding and may predict the deeper processing of the emotional information observed in the 250–1,000 ms time-window after the stimulus onset (Paulmann, 2016; Steber et al., 2020). The time window between 400 and 1,000 ms has been related to the motivational relevance and extensive processing of the prosodic emotional stimulus. In such window, the observation of the Late Positive Potential (LPP) over centro-parietal recording sites is frequent (Steber et al., 2020). The LPP amplitude is higher in emotional than neutral stimuli, while it is shorter during the emotional down-regulation (Pan et al., 2020).

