#### Participants

Typically developed participants will be recruited from a public announcement posted on Tecnologico de Monterrey, Campus Monterrey. Autistic participants will be recruited by contacting parents of autistic children attending San Jose Hospital from Tecnologico de Monterrey.

Sample size estimation was calculated with G^∗^Power software version 3.1.9.7 (Faul et al., 2007) for Cohen’s d effect size index of 0.8, correlations among repeated measures of 0.5, statistical significance set at *p* < 0.05. For level comparisons, results indicated that 20 participants in each group would be enough to provide an estimated power of 0.90. For group comparisons, results indicated that 38 participants in each group would be enough to provide an estimated power of 0.91.

Forty high-functioning autistic volunteers aged 9 to 11-year-old will be involved in this stage of the research. All autistic participants will be diagnosed by a clinician according to DSM-V (Diagnostic and Statistical Manual of Mental Disorders, Fifth Edition) (American Psychiatric Association, 2013) or the International Classification of Diseases and Related Health Problems – Tenth Edition (World Health Organization, 1994) criteria. Autistic symptomatology will be assessed by the Autism Spectrum Rating Scales (ASRS) – parent report (Goldstein, 2012). A T-score greater than 60 (slightly elevated to very elevated scores for autistic behaviors) on Social/Communication, DSM-IV-TR (Text Revision), Peer and Adult Socialization and Social/Emotional Reciprocity domains will be considered as an inclusion criterion.

In addition, 40 TD volunteers aged 9 to 11-year-old will be included in this study. Similar to autistic children, ASRS will be used, and children with a score inferior to 60 in all scales will be included.

Any TD or autistic participant will be excluded if child:

•is under medication affecting the central or peripherical nervous system,•has hearing loss or deficits, and/or•has history of a developmental pathology and/or any disease affecting behavior and nervous system, apart from ASD for autistic participants.

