This project of investigation might encounter some pitfalls and unexpected results. Non-professionalism of actors recruited for emotional recordings during Stage 1 may affect the reliability of required prosodies. Nevertheless, the number of volunteers will be increased in order to generate four times more utterances than necessary to enable the selection of best actor participants. Furthermore, emotion recognition accuracy will be validated by supervised learning algorithm to ensure the quality of emotion discrimination based on acoustic features. Stage 2 aims to explore emotional recognition impairments in autism triggered by naturalness of human voices. We expect to observe a diminution of the amplitude of ERPs in the autistic population as a reflect of decreased attentional, sensorial, and cognitive emotional processing (Lartseva et al., 2015; Lindström et al., 2016, 2018). The autistic condition may also be characterized by hemispheric lateralization anomalies due to lateralized compensatory brain activity (Subbaraju et al., 2018). Impairments are expected to fade with the decreasing naturalness of voice stimuli. However, in the opposite case, no effect of naturalness on neural emotional processing by autistic children would be an evidence that the modulated acoustic parameters would not participate to autistic impairments. In the latter situation, or in case of enhancement of autistic impairments triggered by naturalness modulations, the acoustic edition of the stimuli will be reconsidered. Finally, Stage 3 expects the implementation of less natural voices in a robot-based intervention with the aim of improving emotion detection by autistic children. The 2-week intervention may imply a high rate of withdrawals whereas the sample size needed is relatively high. However, upon completion, we expect the intervention to trigger a reduction of autistic impairments (reduction of symptomatology, higher EEG activity, higher behavioral accuracy for emotion discrimination: smaller reaction times, and higher correct answers at end- and follow-up assessments).

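### Screening ERPs by significance against zero selects on the outcome itself; if both groups must pass, weak autistic responses are lost and the group difference shrinks

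*Protocol article*

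**What the plan says.** In the protocol article, the Stage 2 section Statistical analysis sets a preliminary test of each ERP component by "comparing their mean amplitudes to zero at ROIs using one-sample t-tests". It then says that "Statistically significant ERPs will be considered for further amplitude analysis". The Stage 3 section Statistical analysis on ERPs data repeats the rule and gives the reason: "This method will allow us to focus exclusively on significant responses". For Stage 2 the threshold is given as "level of significance will be set at *p* < 0.05", and Stage 3 uses the same one.

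The Discussion states the expected direction: "We expect to observe a diminution of the amplitude of ERPs in the autistic population". The section EEG Signature of Emotion Recognition also cites a study in autistic adults in which the LPP contrast between emotional and neutral words was not significant in the autistic sample.

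The Stage 3 voice is the one whose autistic MMN, at the ROI with the maximum peak, lies nearest to typical processing of human speech.

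Three points are left open: whether the test against zero is run per group, per level and per deviant or on pooled data; whether an ERP must pass in one group or both; and what happens to a cell of a planned Group × ROI or Level × ROI ANOVA that fails.

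**The concern.** The variable used to decide what is analysed is the same variable that is then compared between groups, and the screen favours large values. A truly small autistic response is the one most likely to fail it. If such a response does pass, it will often be because chance made it look larger. With a screen that both groups must pass, the study would tend to discard the deficit it is looking for, or to understate it. The stated power makes no allowance for this.

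A per-group screen is a natural reading. The Stage 2 Data Analysis section averages ERPs separately for each condition and takes latencies by level and group, and the Level ANOVAs are run within each group. In Stage 3 a screen per session would raise the same problem for a weak response before the intervention: it would be either dropped or overestimated, and an overestimate would understate a later gain.

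**Working it through.** **Inputs from the protocol.** There are 40 autistic and 40 typically developed (TD) children (Stage 2 Participants). There are six blocks, of which each child hears three (Passive Oddball Paradigm). Children per group per level = 40 × 3/6 = 20, assuming blocks are spread evenly. The ROI list gives 18 ROIs. Planning values are "d effect size index of 0.8, correlations among repeated measures of 0.5", so f = 0.8/2 = 0.4.

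**The plan's own power.** For the between factor of a repeated-measures ANOVA, λ = f²·N·m / (1 + (m − 1)ρ), with m = 18 and ρ = 0.5.
- Group comparison: 38 per group × 3/6 = 19 per group, N = 38. λ = 0.16 × 38 × 18 / 9.5 = 11.52; power 0.910 (stated 0.91).
- Level comparison: 20 children × 3 blocks, N = 60, six conditions. λ = 0.16 × 60 × 18 / 9.5 = 18.19; power 0.899 (stated 0.90).

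Both reproduce. The three-of-six reading is inferred, because the article does not print N or m. Neither figure allows for the screen.

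**Chance of passing.** This uses a one-sample t-test, two-sided 0.05 (sidedness is not stated), n = 20 and the noncentral t. The protocol gives no amplitude means or SDs, so the true means below are assumptions.

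| True mean (SD) | 0 | 0.2 | 0.3 | 0.4 | 0.5 | 0.6 | 0.8 | 1.0 |
|---|---|---|---|---|---|---|---|---|
| Passes | 5% | 14% | 25% | 40% | 57% | 72% | 92% | 99% |

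In Stage 3, with 18 per group, a mean of 0.3 SD passes 22%.

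**Group difference among retained results.** One ROI, n = 20 per group, unit SD, 200,000 simulations:

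| Autistic / TD (assumed) | True | Both pass | Either passes | TD passes | Pooled |
|---|---|---|---|---|---|
| 0.3 / 0.8 | 0.50 | 0.26 | 0.52 | 0.53 | about 0.50 |
| 0.5 / 0.8 | 0.30 | 0.19 | 0.31 | 0.33 | 0.30 |
| 0.8 / 1.6 | 0.80 | 0.77 | no loss | no loss | no loss |

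The direction for the autistic amplitude follows from the first row. The groups are independent, so the retained TD mean is 0.3 + 0.53 = 0.83, and the retained autistic mean when both pass is 0.83 − 0.26 = 0.57, against a true 0.30. Surviving autistic amplitudes are inflated; it is the gap that shrinks.

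**All 18 ROIs, ρ = 0.5, 19 per group, true difference 0.8 SD, both groups required to pass at an ROI.**

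| Autistic / TD (assumed) | ROIs kept (mean) | Difference among survivors | Chance of declaring a difference |
|---|---|---|---|
| 0 / 0.8 | 0.8 | 0.80 | 0.91 → 0.22 |
| 0.2 / 1.0 | 2.4 | 0.53 | 0.91 → 0.28 |
| 0.4 / 1.2 | 6.8 | 0.62 | 0.92 → 0.66 |
| 0.8 / 1.6 | 16.3 | 0.78 | 0.91 (almost no loss) |

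In the first row the harm is lost power without shrinkage. With the screen met by either group, power stays at 0.91 to 0.94. A screen pooled over groups at one ROI with n = 20 costs little (0.69 to 0.65 at an autistic mean of 0.2 SD) unless the autistic response is absent (0.69 to 0.43).

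**Voice choice.** Five autistic levels taken as independent, n = 20, TD reference 1.0 SD:

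| Autistic means across levels (assumed) | No voice passes |
|---|---|
| all 0.2 | 48% |
| 0.2 to 0.4 | 22% |
| 0.2 to 0.6 | 5% |
| 0.2 to 1.0 | 0% |

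When at least one level passes, the chosen voice is the same as without the screen in 93% to 98% of runs.

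**The case against.** The strongest objection is that the protocol never says both groups must pass. Its declared aim, to separate real scalp distributions from noise, fits a check that a component exists at a site at least as well as a per-group exclusion. Of the four readings tabulated, only one gives material shrinkage; the others leave the difference unchanged or widen it slightly. The full protocol or analysis plan may settle the scope. This stands. A reader might infer that the group difference is certainly biased toward zero, and the text does not support that.

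A reader might also infer that the screen steers the voice choice toward a falsely typical response. That does not follow either. The rule already seeks the autistic response nearest to typical, so dropping weak responses mostly removes voices that would not have been chosen.

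The amplitudes used here are assumptions. At the protocol's planning difference of 0.8 SD with an autistic mean of 0.8 SD, even the strictest reading does almost no harm.

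Finally, a remedy limited to a few fixed ROIs would go too far. P200 is one of the four components, and lateralisation is a stated interest with its own planned ANOVAs across the scalp.

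What survives is that the rule as written permits the harmful reading, and that the per-condition averaging and per-group ANOVAs make it a natural one. Leaving the scope open also lets the retained set be settled after the data are seen.

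**Conclusion.** The concern holds in conditional form. The rule screens on the outcome in the direction of the hypothesis. If it is applied per group and both groups must pass, with about 20 children per group per level, autistic responses of 0.3 SD are usually dropped and those of 0.5 SD fail 43% of the time (100 − 57). Survivors are overestimated, and the group difference shrinks from 0.50 to 0.26 or from 0.30 to 0.19 (TD assumed at 0.8 SD). Across the 18 ROIs, power can fall from 0.91 to 0.28. If the screen is met by either group, by the TD group or by pooled data, or if autistic responses are about 0.8 SD or larger, there is little or no shrinkage. For the voice choice, the finding is limited to the chance that no voice is eligible when all autistic responses are weak, a case for which the protocol gives no rule. The same wording in Stage 3 needs the same repair, although its size there was checked only for the pass rate.

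**What to change.** Do not let significance against zero in a single group, level or session decide what enters the Group, Level, Session or voice comparisons. There are two acceptable forms:

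1. Drop the screen and report the one-sample tests descriptively.
2. Keep one existence check per component and ROI, applied to the average pooled over groups and levels (in Stage 3, over groups and sessions). Then analyse every group, level and session at the retained ROIs, whether or not each cell is significant.

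The first is the safer choice if autistic responses may be near zero, where even a pooled check can cost power.

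Keep P200 and the planned laterality analyses. Make the voice choice at one ROI, either fixed in advance or identified from the pooled average, with all five levels eligible. The protocol's introduction already supports a fronto-central site for the MMN: "Early automatic auditory perception is usually observed between 100 and 250 ms over frontal and central cortices". Make the matching change in Statistical analysis on ERPs data for Stage 3.

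The cost is a change of analysis wording in two sections, with no effect on recruitment or recording. The downside is that some noisy cells stay in the analysis.
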